#### 2.5.5. Safety Evaluation

Vital signs, adverse events, and severe adverse events will be evaluated before treatment at the following points: week 0, week 2, week 4, week 6, week 8, and during week 16 follow-up period. We will evaluate the blood routine, blood biochemistry, routine urine, and physical examination during the screening period, the 8^th^ week of treatment, and the follow-up period (16^th^ week). We will screen for pregnancy during the initial participant screening (Table 2).

#### 2.5.6. Recurrence Evaluation

All patients who complete the treatment will be followed up for 8 weeks, and the psoriasis area and a PASI score will be recorded. A PASI score that exceeds the baseline score at the time of admission, new pustules, or erythroderma will be considered recurrence. During the follow-up period, if a patient is assessed as having recurrence, the patient will be able to decide whether to end the follow-up and start further treatment.

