## Abstract

*Introduction*. The etiology and pathogenesis of psoriasis are complex. Blood-heat syndrome is the core pathogenesis of psoriasis. Based on theories of Chinese medicine (CM), heat-clearing and blood-cooling (HCBC) are the primary treatment. Very few studies have investigated the pharmacological mechanism of the CM HCBC method for treating psoriasis. This multicenter randomized controlled trial will focus on treating psoriasis blood-heat syndrome with the HCBC method using Jueyin granules (JYKL). This will be an objective and standardized evaluation of the efficacy, safety, and reproducibility of the HCBC method to obtain objective evidence meeting international standards that aim to establish a clinical standard suitable for the popular application of CM for treating psoriasis. *Methods and Analysis*. A five-center randomized double-blind placebo-controlled clinical design will be used in this study. At least 196 participants will be randomly assigned to receive either JYKL or placebo treatment approximately 30 minutes after meals in the morning and evening (one sachet per time, twice daily for 8 consecutive weeks). The study duration will be 17 weeks, including 1 week of screening, 8 weeks of intervention, and 8 weeks of follow-up. The patients will be evaluated every 2 weeks, and the measures will be compared with baseline values. The primary outcome measure will be the psoriasis lesion area severity index. We will also observe the recurrence rate, body surface area, physician global assessment, dermatology life quality index, quality of life index, visual analogue scale score, CM symptom score, combined drug use, and adverse events. This trial is registered with NCT03961230.

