## 2. Methods and Analysis

### 2.1. Study Design

This will be a multicenter randomized double-blind placebo-controlled clinical trial. It will aim to objectively standardize the evaluation of the clinical efficacy, safety, and recurrence of blood-heat syndrome of psoriasis vulgaris treated with HCBC in CM. The results will be helpful for establishing the clinical standard of traditional CM in the treatment of psoriasis. The trial has been registered at NCT03961230. The start and end of recruitment was planned for January 2019 and December 2021, respectively.

Prior to the commencement of the study, the investigators and researchers require uniform training to ensure that the medical staff involved in the study are fully aware of all aspects of the trial. This study will be performed in five centers in China: Yueyang Integrated Traditional Chinese and Western Medicine Hospital, Beijing Traditional Chinese Medicine Hospital, First Affiliated Hospital of Anhui University of Traditional Chinese Medicine, Affiliated Hospital of Gansu University of Traditional Chinese Medicine, and Guangxi Zhuang Autonomous Region Institute of Dermatology Prevention and Control. Competitive enrollment will be applied in all research centers to achieve the goal of 196 total participants. Each participant can be enrolled only once.

Five phases will be included in the study: screening/registration, allocation, treatment/intervention, end of the intervention, and follow-up. During the initial screening, participants will be recruited through dermatology clinics, where they will undergo a physical examination and eligibility assessment. According to the assessment results, a run-in period of up to one week will be required. All patients who are diagnosed with psoriasis with blood-heat syndrome will undergo laboratory blood testing, including a complete blood cell count, liver function test, renal function test, and a pregnancy test before study inclusion. Additionally, routine urine tests, vital sign monitoring, and physical examinations will be performed (Figure 1). Patients who are willing to join the clinical trial will receive study information and consent forms. The consent forms must be signed before a patient will be included in this study.

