### 2.5. Outcome Measures

#### 2.5.1. Primary Outcome

The primary outcome is the reduction in the Psoriasis Area Severity Index (PASI) score, which will be calculated as follows: PASI reduction = (PASI at baseline)–(PASI at week 8 of the treatment period).

The PASI score of the patients will be assessed every 2 weeks during the treatment period and every 4 weeks during the follow-up period. The main result of the RCT will be the percentage of patients whose PASI score decreased by more than 75% compared with the baseline at 8 weeks [2].

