After the Ming and Qing dynasties, “blood-stage treatment” became the primary theoretical basis of syndrome differentiation and the treatment of psoriasis. The epidemiological study of many large samples revealed that the incidence of “blood-heat syndrome” ranked first among all types of psoriasis. JYKL is a CM compound developed based on [name] experimental prescription “XueRe No. 1” and many years of clinical experience. JYKL is clinically used to treat psoriasis vulgaris, especially the blood-heat type. Although traditional medicine provides front-line pharmacotherapy for millions of Chinese individuals, its application is often viewed with skepticism by the Western medical establishment. Therefore, it is necessary to scientifically verify that treatment using JYKL has a curative effect on the psoriasis with blood-heat syndrome and verify that blood-heat syndrome is the core problem to be solved.

Based on the clinical experience with “blood-stage treatment,” this project will objectively and normatively evaluate the clinical efficacy, safety, and control of relapse of the blood-heat syndrome in psoriasis vulgaris treated with JYKL (the representative CM prescription for blood-heat syndrome) through a multicenter double-blind RCT. This will further validate the CM treatment scheme for blood-heat syndrome and psoriasis vulgaris, thereby providing high-level evidence through rigorous research.

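### The recurrence rule counts PASI above the admission score, with no response requirement, so it measures worsening beyond baseline and not loss of response

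*Protocol article*

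**What the plan says.** Section 2.5.6 of the protocol article gives the rule in one sentence: "A PASI score that exceeds the baseline score at the time of admission, new pustules, or erythroderma will be considered recurrence". The same section says who is followed: "All patients who complete the treatment will be followed up for 8 weeks". It attaches a consequence to the event, namely that "the patient will be able to decide whether to end the follow-up and start further treatment". It sets no condition on the week-8 result.

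Recurrence carries weight in the article. The Abstract says "We will also observe the recurrence rate". Section 2.1 states the aim as "evaluation of the clinical efficacy, safety, and recurrence of blood-heat syndrome", and the Discussion says the trial will evaluate "control of relapse of the blood-heat syndrome in psoriasis vulgaris treated with JYKL". Table 2 schedules a recurrence assessment at weeks 12 and 16.

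Section 2.5.1 measures week-8 efficacy against the same admission score, as a difference ("PASI reduction = (PASI at baseline)–(PASI at week 8 of the treatment period") and as a responder rate ("percentage of patients whose PASI score decreased by more than 75% compared with the baseline at 8 weeks").

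**The concern.** Recurrence means losing something that was gained. The rule never looks at what was gained: its threshold is the pre-treatment score, and a patient need not have improved to meet it. That goes wrong in two ways. Responders who lose almost all their improvement are not counted, and patients who never improved are counted once they drift slightly above their starting point.

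The between-arm comparison also suffers. The arm with less improvement at week 8 enters follow-up closer to the threshold and crosses it more often, even if the disease behaves identically in both arms after treatment stops. A lower rate on JYKL could then be reported as control of relapse when it largely reflects the week-8 difference.

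**Working it through.** The article gives no expected recurrence rate, so there is no figure to reproduce. The sample size rests on PASI-50 and is not affected.

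**Step 1. The rule applied to single patients (no assumptions needed).** Share of gain lost = (follow-up − week 8) / (baseline − week 8).

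| Baseline | Week 8 | Follow-up | Share of gain lost | Recurrence under section 2.5.6 |
|---|---|---|---|---|
| 6.0 | 1.0 | 5.9 | 4.9/5.0 = 98% | No |
| 20 | 2 | 20.0 | 18/18 = 100% | No (must exceed baseline) |
| 6.0 | 6.0 | 6.1 | no gain to lose | Yes |
| 20 | 22 | 22 | no gain, no change since week 8 | Yes |

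**Step 2. Effect on the between-arm rate (illustrative).**

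Inputs from the protocol: PASI-50 of 55.66% and 35.3% (section 2.5.3); follow-up PASI at weeks 12 and 16 (section 2.5.1 and Table 2).

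Assumptions, not in the documents:
- Fractional improvement R at week 8 is normal with SD 0.25 to 0.45, capped at 1. Its mean is 0.5 + SD × z(PASI-50 rate), so that P(R ≥ 0.5) equals the protocol's rate.
- PASI as a fraction of baseline is 1 − R at week 8. At each of two follow-up visits it moves by a normal amount with mean 0, 0.1 or 0.2 and SD 0.15, floored at 0. This process is the same in both arms, so the drug has no effect on relapse.
- Recurrence as written is a value above 1 at either visit. Pustules and erythroderma are not modelled.

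Results from 1,000,000 simulated patients per arm and setting:

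| SD of R | Drift per visit | Written rule, JYKL | Written rule, placebo | Responders losing ≥ half their gain, JYKL | Same, placebo |
|---|---|---|---|---|---|
| 0.25 | 0 | 6.0% | 12.8% | 6.2% | 7.2% |
| 0.25 | 0.2 | 34.3% | 49.9% | 59.0% | 62.7% |
| 0.35 | 0.1 | 20.6% | 35.7% | 21.7% | 24.7% |
| 0.45 | 0 | 14.8% | 28.6% | 4.2% | 5.1% |
| 0.45 | 0.2 | 37.5% | 56.1% | 49.4% | 53.7% |

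Over all nine combinations the written rule gives 6.0–37.5% on JYKL and 12.8–56.1% on placebo, a gap of about 7 to 19 points. Loss of at least half the gain among PASI-50 responders differs by about 1 to 4 points. PASI-50 non-responders supply 81–99.6% of the events on JYKL and 90–99.8% on placebo. With a visit SD of 0.18 in place of 0.15, the written rule gives 7.6–38.1% and 15.0–56.4%.

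**Step 3. A different relapse model.** Suppose instead that each patient loses a fraction L of the gain, with L normal (0.6, 0.3). An improved patient then exceeds baseline only if L > 1, with probability 1 − Φ(0.4/0.3) = 0.091. A patient already worse at week 8 stays above baseline if L < 1, with probability 0.909. The share worse than baseline at week 8 under the Step 2 distributions is 1.6% (JYKL) and 5.2% (placebo) at SD 0.25, and 10.5% and 23.2% at SD 0.45.
- SD 0.25: JYKL 0.984 × 0.091 + 0.016 × 0.909 = 10.4%; placebo 0.948 × 0.091 + 0.052 × 0.909 = 13.4%.
- SD 0.45: JYKL 0.895 × 0.091 + 0.105 × 0.909 = 17.7%; placebo 0.768 × 0.091 + 0.232 × 0.909 = 28.1%.

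The gap keeps its direction but shrinks to about 3 to 10 points. In this model 1 − Φ(−0.1/0.3) = 63.1% of responders lose at least half their gain, yet only 9.1% are flagged.

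**The case against.** A reader might infer that the recurrence rate is simply week-8 efficacy counted a second time. The documents do not support that. The event is read at weeks 12 and 16, PASI must be strictly above baseline, and new pustules or erythroderma also count. Change during follow-up therefore contributes. The supportable statement is that the measure is strongly mixed with week-8 response.

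Section 2.5.6 says who is followed, not which denominator the rate will use, and an unseen analysis plan could restrict it. That stands as a caution. It would not cure the threshold, which the article fixes explicitly: even among responders only, a return to exactly the admission score would not count.

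The percentages rest on assumed distributions, and Step 3 shows that their size depends on the relapse model. So does the claim that non-responders supply most events: it holds under additive drift but need not hold where large gains are lost in proportion. The definitional fault in Step 1 needs no model.

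Recurrence is not in the secondary list of section 2.5.2, does not drive the sample size and has no test of its own. PASI at weeks 12 and 16 allows durability to be described in any case. This limits the weight of the point. It does not remove it, because the Abstract names the rate as an outcome and the Discussion promises a conclusion on relapse.

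**Conclusion.** The point holds. As worded, the rule records worsening beyond the admission score, and it does not answer the stated question about control of relapse. That conclusion follows from the text alone.

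The between-arm rate is also confounded with week-8 response. At the protocol's PASI-50 rates, with no drug effect on relapse, the written rule gives roughly 6–38% on JYKL against 13–56% on placebo under the assumed additive drift. Under proportional loss of gain the gap is smaller but in the same direction. These figures show a mechanism and a plausible range; they do not predict this trial's rates. The definition should be changed before the recurrence results are interpreted. The primary outcome and the sample size are untouched.

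**What to change.** Change only how the outcome is counted:

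- **Relapse.** Define it among week-8 responders as loss of a prespecified share (for example half) of the week-8 PASI improvement at week 12 or 16. State in advance whether a responder means PASI-75 or PASI-50. Treat the rate as descriptive, since responders are selected after randomisation.
- **Between-arm durability.** Compare all randomised patients on response at week 8 and maintained at week 16. Count patients who leave follow-up or start further treatment before week 16 as not maintained. This outcome contains week-8 response by design, so a difference shows more sustained benefit and not, by itself, less relapse.
- **Worsening or rebound.** Report PASI above baseline, new pustules and erythroderma separately under that name.
- **Follow-up provision.** Leave the section 2.5.6 text on ending follow-up and starting further treatment as it stands. It then needs its own label, distinct from the relapse outcome.

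The cost is wording and derivation, since PASI at weeks 8, 12 and 16 is already scheduled. The rate becomes less comparable with work using the present definition. The relapse denominator also shrinks: at the protocol's PASI-50 rates, 89 evaluable patients per arm give about 89 × 0.5566 = 50 responders on JYKL and 89 × 0.353 = 31 on placebo, and fewer if PASI-75 is used.

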The BSA, PGA, and VAS will be assessed every two weeks during the treatment period and every four weeks in the follow-up period. The DLQI, QOL, and CMSSS will be assessed by the patients every two weeks during the treatment period. In the follow-up period, the DLQI will only be assessed in the last week (week 16). Laboratory reports will also be monitored until the last visit (Table 2).

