## Figures and Tables

**Figure 1 fig1:**
[figure not shown]
Flow diagram of the study process.

**Table 1 tab1:** Ingredients of Jueyin granules (intervention drug) with English translations.

Common English name	Chinese pinyin	*Genus species* (Latin name)	Plant part
Abalone	*Shi Jue Ming*	*Haliotis diversicolor*	Shell
Honeysuckle	*Jin Yin Hua*	*Lonicera japonica*	Buds or first-blooming flowers
Tree peony	*Mu Dan Pi*	*Paeonia suffruticosa*	Root cortices
Chinese foxglove	*Sheng Di Huang*	*Rehmannia glutinosa*	Root
Snake needle grass	*Bai Huang Sheng Cao*	*Hedyotis diffusa*	Whole grass
Woad	*Da Qing Ye*	*Isatis tinctoria*	Leaf
Wild turmeric	*Yu Jin*	*Curcuma aromatica*	Rhizome

**Table 2 tab2:** Schedule for enrollment, intervention, and assessment.

Activity	Phase	Screen/enroll	Allocation	Treatment/intervention				Intervention end	Follow-up	
	Time points	Week 0		Weeks 1-2	Weeks 3-4	Weeks 5-6	Weeks 7-8		Week 12	Week 16
Screening/enrollment	Eligibility screening	●	●							
	Acquisition of informed consent	●								
	Clinicopathological evaluation	●								
	Medical history recorded	●								
	Enrollment	●								
	Random allocation		●							
	Biological specimen collection		●	●	●	●	●	●	●	●

Treatment/intervention	Basic treatment + JYKL		★-------------------------------------------------------------------------★								
	Basic treatment + placebo granules		☆-------------------------------------------------------------------------☆								

Outcome assessment	PASI score	●	●	●	●	●	●	●	●	●
	Affected BSA	●	●	●	●	●	●	●	●	●
	PGA score	●	●	●	●	●	●	●	●	●
	DLQI score		●	●	●	●	●	●		●
	QOL score		●	●	●	●	●	●		●
	VAS score		●	●	●	●	●	●	●	●
	CM syndrome		●	●	●	●	●	●		●
	Recurrence								●	●

Safety assessment	Vital signs	●	●	●	●	●	●	●		●
	BR	●					●	●		●
	BB	●					●	●		●
	RUT	●					●	●		●
	DC	●	●	●	●	●	●	●		●
	PT	●								
	PE	●					●	●		●
	AEs		●	●	●	●	●	●		●
	Severe AEs		●	●	●	●	●	●		●

✩, intervention in the control group; ★, intervention in the experimental group; ●, what needs to be done in the corresponding time period. JYKL, Jueyin granules; PASI, Psoriasis Area and Severity Index; BSA, body surface area; PGA, physician global assessment; DLQI, dermatology life quality index; QOL, quality of life; VAS, Visual Analogue Scale; CM, Chinese medicine; BR, blood routine; BB, blood biochemistry; RUT, routine urine test; DC, drug combination; PT, pregnancy test; PE, physical examination; AE, adverse event.

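### A patient who recurs and leaves at week 12 has no scheduled adverse-event or drug record after week 8 and no week-16 data, so late secondary and safety comparisons can be selective by arm

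*Protocol article*

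**What the plan says.** Three places in the protocol article bear on this.

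- **Section 2.5.6, who is followed.** "All patients who complete the treatment will be followed up for 8 weeks". Recurrence is then defined: "A PASI score that exceeds the baseline score at the time of admission, new pustules, or erythroderma will be considered recurrence". The section closes with the exit rule: "if a patient is assessed as having recurrence, the patient will be able to decide whether to end the follow-up and start further treatment". It does not say whether assessments continue for a patient who takes that option, and it does not mention patients who stopped treatment early.
- **Section 2.5.5, when safety is assessed.** Vital signs, adverse events and severe adverse events are taken at "week 0, week 2, week 4, week 6, week 8, and during week 16 follow-up period". Week 12 is not listed.
- **Table 2 and section 2.5.2, what happens at week 12.** The visit takes place. Table 2 marks PASI, BSA, PGA, VAS and recurrence there, and section 2.5.2 agrees for three of these: "The BSA, PGA, and VAS will be assessed every two weeks during the treatment period and every four weeks in the follow-up period". The rows for adverse events, severe adverse events and drug combination are blank at week 12 and marked at week 16. DLQI and the safety laboratory tests are also blank at week 12 and taken at week 16.

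**The concern.** Recurrence and safety are stated aims of the trial (section 2.1), and the abstract lists recurrence rate, combined drug use and adverse events among the measures. All three depend on what is collected between weeks 8 and 16.

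The patients offered an exit are those with a PASI above baseline, new pustules or erythroderma, so they are among the worst outcomes by definition. If the granules influence recurrence, the number who leave will differ between arms. The week-16 comparison is then made between two differently selected groups. The first visit at which recurrence is scheduled to be assessed is also the one visit with no scheduled safety or drug entry. An analysis plan written later can choose how to handle missing values, but it cannot recover observations that the schedule never asked for.

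**Working it through.** **Step 1. Set the week-12 and week-16 columns of Table 2 side by side.**

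| Item | End of intervention | Week 12 | Week 16 |
|---|---|---|---|
| PASI, BSA, PGA, VAS | yes | yes | yes |
| Recurrence | no | yes | yes |
| DLQI | yes | no | yes |
| Blood routine, biochemistry, urine | yes | no | yes |
| Drug combination | yes | no | yes |
| Adverse events, severe adverse events | yes | no | yes |

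The list of time points in section 2.5.5 matches the adverse-event rows. Two independent places agree, so the blank cells are not a table-reading artefact.

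**Step 2. Trace a patient who recurs at week 12 and ends follow-up.**

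- Kept: everything to week 8, the week-12 PASI, BSA, PGA and VAS, and the recurrence event.
- Not scheduled: any adverse-event, severe adverse-event or drug record after week 8.
- Lost: week-16 PASI, BSA, PGA, VAS, DLQI and laboratory tests.

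A patient whose recurrence is first found at week 16 loses nothing, because that is the last visit. The exit rule therefore matters at week 12, or at an unscheduled visit before week 16.

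**Step 3. Patients who stay.** Their next scheduled adverse-event and drug entry after week 8 is at week 16, an interval of 16 − 8 = 8 weeks. With a week-12 entry it would be 4.

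**Step 4. Size, as an illustration.** Section 2.5.3 gives 98 per arm, which is 89 × 1.10 = 97.9, and allows 10% loss. The article gives no recurrence or exit rate, so these are assumptions.

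- Entering follow-up, if the 10% loss is taken as non-completion: 98 × 0.90 = 88.2 per arm.
- Losing week-16 data = 88.2 × (recurrence by week 12) × (share who leave).
- Control, 20% recur and half leave: 88.2 × 0.20 × 0.5 = 8.8.
- Granules, 10% recur and half leave: 88.2 × 0.10 × 0.5 = 4.4.
- Remaining at week 16: 79.4 against 83.8, or 81.0% against 85.5% of the 98 randomised.

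The range per arm is wide:

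| Recurrence by week 12 | Share who leave | Remaining at week 16 | Share of 98 |
|---|---|---|---|
| 10% | 25% | 86.0 | 88% |
| 20% | 50% | 79.4 | 81% |
| 30% | 50% | 75.0 | 77% |
| 40% | 100% | 52.9 | 54% |

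**The case against.** The strongest reply is that the damage is limited, and much of that reply stands.

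- **Primary outcome.** A reader might infer that the main result is biased. It is not. The article fixes it at week 8, as the "percentage of patients whose PASI score decreased by more than 75% compared with the baseline at 8 weeks", before follow-up begins.
- **Recurrence count.** A reader might infer that patients who leave disappear from the recurrence rate. They do not. The option opens only after recurrence has been assessed, so the event is already counted, and the week-12 scores are scheduled at the same visit.
- **Early stoppers.** The article does not expressly exclude them from follow-up. Section 2.5.6 is about evaluating recurrence, and the full protocol may cover the rest. What stands is the plain reading: the only follow-up population described is patients who complete treatment, so as written the recurrence rate is calculated over completers.
- **Adverse events in weeks 8 to 12.** It would be too strong to say that they are lost entirely. Volunteered or serious events may still be recorded under reporting rules that an article need not repeat, and patients who stay can report earlier events at week 16. What the documents show is that no assessment is scheduled at week 12.
- **Response credited to the wrong drug.** This is tempting but weak. A patient who recurs by PASI has a score above baseline, so there is no maintained response to misattribute. Patients who stay have drug use recorded at week 16.
- **No contradiction.** Section 2.5.5 and Table 2 agree, so leaving week 12 out is a design choice and not an inconsistency. That is true, but it does not answer what happens when the choice meets the exit rule.

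**Conclusion.** The point holds as a limited one. Followed as written, the schedule leaves outcome-dependent gaps in two places: the week-16 secondary measurements, and the adverse-event and drug record after week 8. Both fall on patients who recur and leave, in numbers that can differ by arm if the treatment affects recurrence. In addition, the recurrence rate has completers as its denominator, so it is not a comparison of all randomised patients.

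The size cannot be fixed from the documents. About 9 against 4 patients is an illustration. It rests on 88 per arm entering follow-up, on recurrence of 20% against 10%, and on half of those leaving; only the 98 per arm and the 10% loss come from the article. The conclusion needs none of these figures, only that some patients recur by week 12 and take the option offered. This is a cheap improvement to secondary and safety data and does not threaten the main result.

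**What to change.** 1. In Table 2, add week-12 marks for adverse events, severe adverse events and drug combination, and add week 12 to the time points in section 2.5.5. Take the same record at any exit visit.
2. In section 2.5.6, state that all randomised patients who agree are assessed through week 16, whether or not they completed treatment, recurred or started further treatment. Record the start date of any further treatment.

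These changes concern data collection only. The patient's choice about further treatment is untouched, and no clinical rule is altered. The cost is a minor amendment and extra case-report pages at a visit that already takes place, with slightly more site work for patients who stopped or relapsed. Patients already past week 12 cannot be given the missing entry retrospectively, so the change is worth more the earlier it is made.
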